#### Blinding/masking

It is not possible to blind patients regarding the result of randomisation in this type of intervention. While it is not possible to blind the health professionals administering the orientation program, they will have no involvement in assessing and analysing the data.

### Intervention

The intervention is a Multidisciplinary Orientation Program. It will be run twice weekly in the oncology out-patients department, and comprises a 5 minute 'virtual hospital tour', a talk by a registered nurse giving an overview of potential side effects of radiation therapy and chemotherapy, and an opportunity to meet the health care team. The hospital tour highlights areas of the hospital that patients are likely to need during the course of their treatment, such as the pharmacies and the pathology department. It also will show practical areas such as the Food Court, Post Office and Automatic Teller Machines. Different parts of the Cancer Care Services building are shown - the check in desk, the different waiting areas, the day therapy unit and the radiation treatment floor. The side effects overview will include common side effects experienced by oncology patients and self care strategies. This talk was developed using the information currently given to patients in the respective treatment areas at the start of their treatment, but does not include details of specific treatment regimens.

The health care team consists of a nurse, a cancer care coordinator, a social worker, a occupational therapist, a physiotherapist, a speech pathologist and a discharge coordinator. The healthcare team each will have five minutes to give an overview of their role, how they may support the patients throughout their treatment and encounter at the cancer care centre and to give patients their contact details. The health care team each have their scripts and powerpoint slides prepared to ensure the consistency of each sessions. All patients attending the intervention will be given a 10-page booklet which contains the information given in the 'virtual tour' and expands on it, eg. prices for car parking, access to public transport, opening times for food outlets within the hospital, note space. It also has information about the role of each member of the health care team, telephone numbers for clinics, and tips for getting through treatment. At the end of the session there will be time for questions for both the nurse and the members of the healthcare team. Powerpoint presentation and a projector will be used to facilitate every section of the program. Scripts and notes have been designed and agreed by the health care team and will be used to ensure the consistency of each session.

### Measures

#### Anxiety

Anxiety will be measured using the trait anxiety version of the Spielberger's Trait Anxiety Inventory (STAI) and the Brief Profile of Mood States - Total Mood Disturbances Score (POMS-TMDS) [35-37].

The STAI was developed as a tool for investigating anxiety in normal adults, but has been used extensively for assessing anxiety in cancer patients [10,11,21,33]. The scale consists of 20 questions yielding a measure of state anxiety (S-Anxiety) which assesses how a patient feels generally. An extra 20 questions refer to trait anxiety (T-Anxiety) which refers to individual differences in "anxiety-proneness" [35]. The STAI demonstrated good psychometric properties [35]. Reliability has been substantiated by means of test-retest correlations (r = 0.65-0.86) and Cronbach's alpha (median coefficient of 0.90). Scores on the scales can range from 20-80, with higher scores indicating more symptoms of anxiety [21].

The POMS-TMDS is a shorter version of the 65 item Profile of Mood States (POMS) [37]. It consists of 11 items that yield a total mood disturbance score that correlates highly (r = 0.93) with the longer POMS which has been utilised extensively for the cancer population [10,11,33,38]. Reliability and validity testing has been carried out successfully in patient with cancer [39]. Permission for use has been granted by the author.

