## Background

There is a consensus that diagnosis and treatment of cancer contributes to psychological distress and anxiety among patients [1-3]. The literature has demonstrated that information can reduce distress by enhancing patients' sense of control. An enhanced sense of control, in turn, relieves anxiety and enhances management of illness [4]. Although the need for information exists across the continuum of cancer care [5,6] the anxiety can be particularly pronounced at the initial visit to a cancer centre [7,8]. Factors contributing to this anxiety and distress can be the lack of familiarity with the environment and with the care providers.

Researchers have investigated interventions with the aim of reducing the anxiety and distress levels among cancer patients [4,9]. One of these interventions includes orientation programs for patients who are newly registered to a cancer service. A study of 150 new cancer patients by McQuellon and research team reported that their orientation was effective in reducing anxiety, distress and depressive symptoms and enhanced knowledge and satisfaction of care [10]. In 2003, Gallant (2003) tested different methods of delivering an orientation program and found that it was more challenging to recruit patients for the face to face arms compared to the mail group [11]. The components of these orientation programs vary and generally include question and answer sessions, a clinic tour, description of procedures, provision of information. However, none of these studies have investigated the effects of orientation programs and were not conducted by a multidisciplinary team.

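### The STAI outcome is specified as the trait form, which the article itself describes as proneness to anxiety: a poor match for the effect of one orientation session, in a section that also confuses the two forms

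*Protocol article*

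**What the plan says.** The opening sentence of the Anxiety section under Measures names the form: "Anxiety will be measured using the trait anxiety version of the" STAI, alongside the "Brief Profile of Mood States - Total Mood Disturbances Score (POMS-TMDS").

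The same section then describes both STAI forms. Of the first it says: "The scale consists of 20 questions yielding a measure of state anxiety (S-Anxiety) which assesses how a patient feels generally". A further 20 questions concern "trait anxiety (T-Anxiety) which refers to individual differences in" anxiety-proneness.

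Data collection has the STAI completed at recruitment (T1), on the first treatment day (T2) and on the seventh treatment day (T3). Analysis compares mean STAI, POMS and CASE-cancer scores between arms by repeated-measures ANOVA.

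On the target of the programme, the Background says that "the anxiety can be particularly pronounced at the initial visit to a cancer centre", and it names unfamiliarity with the environment and with the care providers as possible contributors. Study population describes one orientation session before treatment begins. The hypothesis in the Abstract (Methods) covers anxiety, distress and self-efficacy.

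**The concern.** The programme shows patients the building, introduces the team and explains side effects. It is meant to ease the anxiety of arriving somewhere unfamiliar to start treatment. By the article's own definition, the form named as the outcome asks how prone a person is to anxiety. A scale of that kind may register little of what one session changes between recruitment and the seventh day of treatment.

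Two things are at stake. If the trait form is used and shows no difference, the reader cannot tell an ineffective programme from a scale that does not follow the anxiety in question. Separately, the section describes the two forms so loosely that staff could not be sure which one is intended, while its one explicit instruction points to the trait form.

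**Working it through.** **Step 1. Which form is specified, and how is it used?** These statements can be set side by side:

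- Anxiety section, opening sentence: the trait version is the measure.
- Anxiety section, descriptions: trait anxiety is proneness; state anxiety is how a patient feels in general.
- Data collection: STAI at T1, T2 and T3.
- Analysis: STAI means compared between arms over time.

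The only sentence that selects a form selects the trait form. No sentence makes the state form the outcome. Three administrations and a between-arm comparison over time make the STAI an outcome, not merely a baseline covariate.

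**Step 2. Does it match the target?** The Background links the anxiety to an occasion (the first visit) and to circumstances (place and staff not yet known). The intervention is a single session before treatment, and the last assessment is on treatment day seven. A measure of how a patient feels on the occasion fits this; a measure of individual differences in proneness fits it poorly.

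**Step 3. Does another measure fill the gap?** The brief POMS yields a total mood disturbance score, which bears on distress but is not specific to anxiety. CASE-cancer measures self-efficacy. The STAI is therefore the only anxiety-specific scale.

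**Step 4. What could it cost in power?** Sample size and power gives 375 per arm for 90% power but no effect size or SD, so 375 cannot be reproduced from stated inputs. It can only be solved backwards. Reading the 95% confidence interval as a two-sided 5% test, with a normal approximation for two means:

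d = (1.960 + 1.282) × √(2/375) = 3.242 × 0.0730 = 0.237 SD

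For an assumed STAI SD of 8 to 12 points (the article gives none), this is 0.237 × 8 = 1.9 to 0.237 × 12 = 2.8 points.

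Let f be the share of that effect that the trait form registers. This is an assumption; the article gives no value. Then

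power = Φ( f × 0.237 / √(2/n) − 1.960 )

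| f | Power, 375 per arm | Power, 51 per arm (pilot) |
|---|---|---|
| 1 | 90% | 22% |
| 0.75 | 68% | 14% |
| 0.5 | 37% | 9% |
| 0.25 | 13% | 5% |

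For f = 0.5 at 375 per arm: 0.5 × 0.237 / 0.0730 = 1.62; 1.62 − 1.96 = −0.34; Φ(−0.34) = 0.37. For the pilot at f = 1: √(2/51) = 0.198; 0.237 / 0.198 = 1.20; 1.20 − 1.96 = −0.76; Φ(−0.76) = 0.22.

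The required sample size grows with 1/f². Restoring 90% power at f = 0.5 would take about 375 / 0.25 = 1,500 per arm.

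The table is for a simple comparison of two means, not for the planned repeated-measures ANOVA. It shows how sensitive power is to lost responsiveness; it does not estimate the trial's actual power.

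**The case against.** The strongest reply is that the authors may have meant the state form, or both. The section calls the whole instrument a trait inventory, presents the 20 state questions as the scale itself, treats the trait questions as additional, and uses a dispositional word for state anxiety. This stands as a caution: the article does not prove a deliberate choice of the trait form. It does not remove the problem, because the one sentence that selects a form is explicit and the section needs correcting either way.

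A second reply is that the article never says the trait score is stable. Its test-retest range (0.65 to 0.86) is not split by form, and no responsiveness data are given. This also stands. Poor fit follows from the article's definition of trait anxiety; a particular degree of insensitivity does not.

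Third, a reader might infer that the main hypothesis cannot be answered. The article does not support this. Distress and self-efficacy are also in the hypothesis, and both are measured at all three times by POMS and CASE-cancer. Only the anxiety part is weakened. Nor does the Background say that anxiety peaks at the first visit; it says that it can be particularly pronounced then.

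Fourth, a reader might take 13% to 37% as the trial's real power. Those values rest on an assumed f of 0.25 to 0.5, applied to a back-solved effect, at the size of the full trial. The current proposal is a pilot of 102 patients meant to evaluate the design and process. Its power is low whichever form is used.

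**Conclusion.** The point holds in a limited form. As written, the anxiety-specific outcome is a scale that the article defines as proneness. That is poorly matched to anxiety linked to the first visit and an unfamiliar setting, and to one session assessed up to treatment day seven. The section is also internally confused about the two forms.

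The consequence is that a null STAI result would be hard to interpret for the anxiety part of the hypothesis. The size is uncertain because the power loss depends on an assumed f: at 375 per arm, power would be about 68% at f = 0.75 and about 37% at f = 0.5. The direction is clearer than the size. The detectable difference is already small, about 0.24 SD, so even a modest loss of responsiveness would cost a good deal of power. For the pilot, the case for the change rests on choosing and testing the right instrument, not on power.

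**What to change.** - Reconcile the Anxiety section so that it names one STAI form as the outcome. Make this S-Anxiety (20 items) at T1, T2 and T3.
- Collect T-Anxiety, if at all, at T1 only, as a baseline covariate.
- Correct the two scale descriptions and the instrument's name so that state and trait are clearly separated.

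The cost is small. One 20-item form replaces another within the same instrument, so the burden at T2 and T3 is unchanged; keeping the trait form as a covariate adds 20 items at T1. The article does not give recruitment status. If any patients have already completed the trait form, their STAI scores should not be pooled with state scores.

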#### Self -efficacy

The communication and attitudinal self-efficacy scale for cancer (CASE-cancer) has been selected to measure self-efficacy in the patients [19]. The CASE-cancer is a psychometrically sound tool with high internal consistency and construct validity. The scale items are performed similarly across literacy levels. It is also recommended for testing the effect of interventions to improve communication, education and involvement in cancer [19]. Permission for use has been granted by the author.

#### Evaluation of Oncology Clinic Questionnaire (EOCQ)

The research team has designed a tool which will specifically investigate whether patients have received particular information prior to their first treatment day (Yes/No). It has included a list of information that the research team believes to be important for patients before they commence their cancer treatment. This tool will be administered at Time 2 and Time 3.

### Data collection

Participants will be asked to complete a series of questionnaires at the time of recruitment (T1), on the day of first treatment (T2), and on the seventh day of treatment (T3) which will measure patients' self-efficacy (CASE) and anxiety (STAI and POMS) at the three time points. Additionally, demographic information will be collected at T1 and the EOCQ will be collected at T2 and T3.

### Sample size and power

A sample size of at least 375 in each arm of the study would be sufficient to achieve a power of 90% using 95% of confidence interval to detect a difference in the anxiety and self-efficacy scores between control group and intervention group. Assuming that approximately 25% fail to consent and a further 10% will be lost to follow-up; an additional 132 in each group will be required and the final sample will require 1,014 patients. In order to evaluate the research design and process, the current proposal is for a pilot study with 10% of the final sample (ie 102 patients, 51 in each arm). According to the statistics of RBWH Cancer Care Services, 274 new cancer outpatients receiving treatment each month. Thus, the sample size proposed is achievable over a period of 12 weeks based on our conservative estimation.

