### Study population

All cancer patients newly registered at a tertiary cancer care centre in Brisbane, Australia, who meet inclusion criteria will be invited to participate in the trial. Patients who consent will be randomly allocated to either the control group, who will receive normal treatment education at the start of their treatment, or the intervention group, who will receive the normal treatment education and will also attend the Orientation Program education session conducted by the multi-disciplinary team, prior to starting their treatment.

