#### Allocation concealment/implementation

After the research nurse has obtained the patient's consent, he/she will telephone a contact who is independent of the recruitment process for allocation concealment. Subsequently, baseline data will be collected. All questionnaires are self-administered by patients. Therefore, the research nurse will not have involvement in completing these questionnaires.

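### The planned total of 1,014 adds non-consent and loss to follow-up together inside the arms, so it is neither the number to randomise nor the number to approach for 375 evaluable per arm

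*Protocol article*

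**What the plan says.** All the figures are in the Protocol article, Sample size and power. The base is "A sample size of at least 375 in each arm of the study", described as "sufficient to achieve a power of 90% using 95% of confidence interval". Two allowances follow: "Assuming that approximately 25% fail to consent", and "a further 10% will be lost to follow-up". The section then states that "an additional 132 in each group will be required and the final sample will require 1,014 patients". The pilot now proposed is set at 10% of that total, given as 102 patients with 51 in each arm.

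Two other sections fix the order of events. Study population says: "Patients who consent will be randomly allocated to either the control group". Allocation concealment/implementation says: "After the research nurse has obtained the patient's consent, he/she will telephone a contact who is independent of the recruitment process". Consent therefore comes before allocation.

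**The concern.** The two allowances act at different stages. Refusal happens before randomisation and determines how many eligible patients must be approached. Loss to follow-up happens after randomisation and determines how many must be allocated to leave 375 evaluable. The plan merges them into one addition to each group, so its total has no clear denominator. A patient who refuses is never in a group and cannot be part of a per-group allowance.

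The method of inflation is also wrong. To end with 375 after a proportional loss, one divides by the proportion retained. Adding the lost percentage to 375 leaves too few.

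At stake is what 1,014 tells the trial team to do. As a randomisation target it enrols more patients than the assumptions require. As an approach target it falls short of the stated minimum. The pilot size is taken from the same total.

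**Working it through.** **Inputs.** From Sample size and power: 375 evaluable per arm, 90% power, 25% non-consent, 10% loss, 132 added per group, 1,014 in total, pilot of 102 (51 per arm). From Study population and Allocation concealment/implementation: only consenters are allocated. Assumed here for the power figures only: a two-sided 5% two-sample comparison. The plan gives neither sidedness nor an effect size or standard deviation.

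**Step 1: reproduce the plan's figure.**
- 375 × (0.25 + 0.10) = 131.25, rounded up to 132.
- 375 + 132 = 507 per arm, and 2 × 507 = 1,014. Exact match.
- Compounding instead, 375 × 1.25 × 1.10 = 515.6, rounded up to 516, would add 141 per arm and not 132. The additive route is the one used.

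**Step 2: apply the plan's own rates in sequence.**
- To randomise: 375 / 0.90 = 416.7, so 417 per arm and 834 in total.
- To approach: 834 / 0.75 = 1,112.

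**Step 3: the other reading of the 10%.** If both percentages are of all patients approached, 65% of those approached are evaluable.
- To approach: 750 / 0.65 = 1,153.8, so 1,154.
- Consenting and randomised: 1,154 × 0.75 = 865.5, about 866.

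On this reading too, 1,014 matches neither number.

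**Step 4: what 1,014 delivers (rates in sequence).**

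| Meaning of 1,014 | Randomised | Evaluable | Evaluable per arm | To approach |
|---|---|---|---|---|
| Randomised | 1,014 | 1,014 × 0.90 = 912.6 | about 456 | 1,014 / 0.75 = 1,352 |
| Approached | 1,014 × 0.75 = 760.5 | 760.5 × 0.90 = 684.5 | about 342 | 1,014 |

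In the first row, 1,014 − 834 = 180 more patients are randomised than needed. In the second, 342 / 375 = 0.912, about 9% short.

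**Step 5: power.** If 375 per arm gives 90% power, power at m per arm is Φ(√(m/375) × (1.960 + 1.282) − 1.960). The effect size cancels.
- m = 342: Φ(0.955 × 3.242 − 1.960) = Φ(1.136), about 87%.
- m = 456: Φ(1.103 × 3.242 − 1.960) = Φ(1.615), about 95%.

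**Step 6: the pilot.**
- 10% of 1,014 = 101.4, given as 102. By comparison, 10% of 834 = 83.4.
- If 102 are randomised, as 51 in each arm implies, 102 / 0.75 = 136 must be approached, and 102 × 0.90 = 91.8 are evaluable, about 46 per arm.

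**The case against.** The strongest defence is that little depends on this figure now. The study proposed is a pilot of 102 patients to evaluate design and process, with no power claim of its own. The 1,014 is a planning figure for a later trial, resting on an approximate consent rate that the pilot can itself observe. No analysis of the current study changes. This stands, and it limits the severity.

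A reader might infer that the main trial is underpowered. The documents do not support that as the leading reading. The allowance is added in each group and the pilot is given per arm, and both describe allocated patients. If 1,014 are randomised, the target of at least 375 is exceeded. The shortfall arises only if 1,014 is the number approached, and then it is about 3 power points.

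A reader might also infer that the pilot's 102 could be patients approached. The statement of 51 in each arm, with allocation restricted to consenters, points to randomised patients. What remains is that 102 is justified as a tenth of a total that contains refusers. Since the pilot has no stated precision or power criterion, 102 against about 84 has no demonstrable consequence.

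It could also be said that an article condenses the full protocol. That does not help here: the objection is to a figure that is stated and to the way it was obtained, and nothing is alleged to be missing.

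**Conclusion.** The point holds at moderate severity. The inflation is wrong as written: the two rates are added, and the non-consent allowance sits inside the arms, contrary to the plan's own order of consent and allocation. With losses in sequence, 375 evaluable per arm needs 834 randomised and about 1,112 approached. If both rates are of all patients approached, the number to approach is about 1,154.

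On the more natural reading, the consequence is 180 surplus randomised patients and an unstated need to approach about 1,352. On the other, it is about 342 evaluable per arm and about 87% power. The patient counts rest only on the plan's own rates. The power figures also rest on a two-sided 5% two-sample comparison, whereas the Analysis section plans repeated-measures ANOVA. For the same reason, the standardised difference that can be back-calculated from 375 per arm (about 0.24) is not the sponsor's design assumption and should not be printed as one.

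**What to change.** Replace the inflation sentence in Sample size and power with wording such as: *375 evaluable patients per arm are required; allowing 10% loss to follow-up, 417 per arm (834 in total) will be randomised; allowing 25% non-consent, about 1,112 eligible patients will be approached.* If the 10% was meant as a share of all patients approached, say so and use about 1,154 approached and about 866 randomised.

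Describe the pilot's 102 (51 per arm) as patients randomised, give about 136 as its number to approach, and stop justifying it as 10% of a total that includes refusers.

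The cost is one paragraph of wording. The effect on main-trial recruitment depends on what 1,014 was meant to be:
- If randomised, both numbers fall: randomised from 1,014 to 834, approached from about 1,352 to 1,112.
- If approached, both rise: approached from 1,014 to 1,112, randomised from about 760 to 834.

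The pilot's size need not change.
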